### Data statement and management

Radiographs selected for the study will be anonymised in accordance with OUH NHS Foundation Trust information governance protocol and uploaded to the secure image viewing platform (www.raiqc.com). Access to the radiographs will be controlled via the study platform using separate user accounts for each reader.

All study data will be entered into a password-protected and secure database. Individual reader accuracy scores will be anonymised, and the study team will not have access to the identifying link between the participants’ personal details and the data. Data about the participants’ seniority level and professional group will be retained to allow group comparisons.

### Sample size and power calculation

The study’s sample size of 500 images, evenly split between normal and abnormal cases, was determined using the Multi-Reader Sample Size Program for Diagnostic Studies. This tool, developed by Hillis,^20^ is specifically designed for MRMC study power calculations. Based on parameters derived from our previous MRMC study on pneumothorax detection, the programme calculated that with 18 readers and 500 cases, our study will achieve 85% power to detect a 10% difference in accuracy between unassisted and AI-assisted readings, with a 5% type 1 error rate (See output from software below).

The chosen sample size of 500 images ensures sufficient statistical power and adequate representation of fracture types and anatomical locations. This robust sample size, combined with our substantial and diverse reader pool, should enable the detection of clinically significant improvements in fracture detection accuracy and allow for subgroup analyses across specialties and experience levels. By using this rigorously calculated sample size, we aim to produce statistically robust and clinically relevant results that can inform the potential integration of AI assistance in fracture detection across various clinical settings, while adequately addressing our study objectives and maintaining statistical validity.

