The difference in diagnostic characteristics (sensitivity, specificity, accuracy, area under the receiver operating characteristic (ROC) curve) of readers as compared with ground truth with and without AI assistance will be the primary outcome on a per image and per abnormality basis. The main analysis will be performed as a single pooled analysis including all groups and sites. Secondary outcomes will include comparison between the performance of subgroups by specialty (emergency medicine, trauma/orthopaedics, physiotherapy, nurse practitioner, radiologist, radiographer), level of seniority (senior, middle grade, junior), degree of difficulty of the image and by anatomical region. Reader-reported confidence with and without the AI assistance will be compared. Secondary outcomes include the diagnostic characteristics of the AI algorithm alone. Surveys will be conducted throughout the study to measure the satisfaction, adoption and confidence in the AI algorithm of the study participants. Per-patient sensitivity will be defined as the proportion of reads in which all true fractures were marked as a proportion of the reads having at least one fracture. Per-patient specificity will be defined as the proportion of reads in which no fracture was marked by the reader as a proportion of the reads that did not show a fracture. These definitions disregard the detection of multiple fractures thus we will define the fracture-wise sensitivity as the proportion of fractures correctly detected as a proportion of all fractures. The two coprimary outcomes will be patient-wise sensitivity and patient-wise specificity. The stand-alone algorithm performance will be assessed by calculating the area under the curve (AUC) of the ROC and free-response ROC curves plotted with their variance. To account for correlated errors arising from readers interpreting the same images with and without AI, the Obuchowski and Rockette, Dorfman-Berbaum-Metz^22^ procedure; a modality-by-reader random effects ANOVA model will be used for estimation. Analyses will be carried out using R and the MRMCaov library.

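### The only stated power, 85%, is for accuracy on 500 images; it does not carry over to the two co-primaries, sensitivity and specificity, which rest on about 250 images each

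*Protocol article*

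**What the plan says.** Under Sample size and power calculation, the protocol article gives one power statement: "85% power to detect a 10% difference in accuracy between unassisted and AI-assisted readings". It is computed "with 18 readers and 500 cases", the cases being "evenly split between normal and abnormal cases", and "with a 5% type 1 error rate". The inputs are described as "Based on parameters derived from our previous MRMC study on pneumothorax detection". The next paragraph concludes: "The chosen sample size of 500 images ensures sufficient statistical power".

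Under Statistical analyses, the primary outcome is stated twice. One sentence counts four measures as primary (the quote stops just before it says so): "sensitivity, specificity, accuracy, area under the receiver operating characteristic (ROC) curve) of readers as compared with ground truth with and without AI assistance will be". Later in the same section: "The two coprimary outcomes will be patient-wise sensitivity and patient-wise specificity". The paragraph on the Obuchowski-Rockette model also says that sensitivity and specificity are what will be tested, with readers and cases both random.

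**The concern.** The power figure belongs to a measure that is not one of the two named co-primaries. By their definitions in the article, patient-wise sensitivity is estimated from fracture images only and patient-wise specificity from non-fracture images only, so each uses about half of the 500. A power computed for a measure that averages over all 500 is not the power of either test.

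The effect sizes differ as well. In a 50:50 set, a 10-point gain in the proportion of correct reads needs sensitivity and specificity gains that sum to 20 points. If AI adds 10 points of sensitivity and leaves specificity unchanged, accuracy moves by only 5 points.

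The interpretation of the result is at stake. A reader of the published claim could take a non-significant sensitivity or specificity result as evidence against a 10-point effect, believing that the study had 85% power to find one.

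**Working it through.** **Inputs from the article.** 18 readers; 500 images, half with fracture; type I error 5% (two-sided assumed, as sidedness is not stated); 85% power; a 10% difference in accuracy.

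**Assumptions.** Accuracy is the proportion of reads that are correct, scored as for patient-wise sensitivity and specificity. The 10% is absolute, that is, 10 percentage points. Neither is stated.

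**The stated 85%.** It cannot be reproduced. The Obuchowski-Rockette calculation needs reader-by-AI and error variances and covariances, and the text gives none. The standard error that the claim implies can be back-solved:

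- z(0.975) + z(0.85) = 1.960 + 1.036 = 2.996
- SE of the accuracy difference = 10 / 2.996 = 3.34 points (3.14 points with a t reference on 17 df; the powers below change by no more than about 0.2 points).

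**A bound that needs no variance components.** At 50% prevalence, accuracy = (Se + Sp)/2. Therefore

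SE(ΔAcc) ≤ [SE(ΔSe) + SE(ΔSp)] / 2,

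with equality only when the two effect estimates are perfectly positively correlated. At least one co-primary thus has an SE no smaller than that of accuracy. At the same alpha and comparable degrees of freedom, its power for a 10-point change is at most 85%.

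**Size under equal variances.** Let v be the total variance (reader and case parts together) of each co-primary's effect estimate, and ρ the correlation between the two estimates. Then

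- Var(ΔAcc) = v(1 + ρ)/2, so SE(ΔSe) = SE(ΔAcc) × √[2/(1 + ρ)]
- Power at 10 points = Φ(2.996 / √[2/(1 + ρ)] − 1.960)

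| ρ | Variance ratio 2/(1+ρ) | SE (points) | Power for 10 points | Difference detectable with 85% power (points) |
|---|---|---|---|---|
| −0.5 | 4.00 | 6.67 | 32% | 20.0 |
| 0 | 2.00 | 4.72 | 56% | 14.1 |
| 0.5 | 1.33 | 3.85 | 74% | 11.5 |
| 1 | 1.00 | 3.34 | 85% | 10.0 |

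For example, at ρ = 0: Φ(2.996/1.414 − 1.960) = Φ(0.159) = 0.563.

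**The 5-point case.** For a 5-point accuracy change, power is Φ(2.996/2 − 1.960) = Φ(−0.462) = 32%.

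**Sensitivity to the assumptions.**

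- *Unequal variances.* At ρ = 0 with a 3:1 variance ratio, Var(ΔAcc) = (3v + v)/4 = v. The less variable co-primary keeps 85% power and the other has Φ(2.996/√3 − 1.960) = 41%.
- *Relative 10%.* With an assumed baseline accuracy of 0.80 the effect powered is 8 points. At ρ = 0 and equal variances, power for a 10-point change is then Φ(2.996 × 10/(8√2) − 1.960) = 75%. With an assumed baseline of 0.70 (7 points) it is 86%.

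**The case against.** The strongest reply is that no particular lower figure is established. The planned model treats readers as random, and the reader-by-AI component depends on the 18 readers; it does not grow because there are fewer images. Suppose that component is held at its value for accuracy and only a share f of the variance doubles when cases fall from 500 to 250. Power is then Φ(2.996/√(1 + f) − 1.960): 85% at f = 0, 76% at 0.25, 69% at 0.5 and 56% at 1. This stands as a reason not to quote 56% as the power of the design. It does not restore the 85%. Under equal variances, holding the reader component fixed amounts to assuming that readers' sensitivity and specificity gains move together perfectly. If AI prompts shift thresholds, so that one rises as the other falls, the correlation is negative and power drops below 56%.

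Second, accuracy may mean AUC. The Outcome measures section lists AUC and not accuracy, and the software output to which the sample size text refers is not in the text at hand. On that reading the conversion above does not apply. AUC is still not one of the two co-primaries, so the mismatch remains.

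Third, accuracy is not wholly outside the primary set, because one sentence includes it. This is correct, but that sentence conflicts with the co-primary sentence in the same section and gives no power for sensitivity or specificity.

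A reader might also infer a joint power of about 32% (0.563²) for both co-primaries. That needs independent effects and a rule that both must succeed, and the article states no such rule. Nor does taking inputs from a pneumothorax reader study show the figure to be wrong. The source is disclosed, and the direction of any error is unknown.

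**Conclusion.** The concern holds as an endpoint mismatch. The article attaches its only power figure to accuracy, names sensitivity and specificity as co-primaries, and then asserts that power is sufficient. If accuracy is the proportion correct and 10% is absolute, 85% is a ceiling for at least one co-primary, reached only in a limiting case. With equal variances the plausible span is wide: about 32% at correlation −0.5, 56% at 0, 74% at 0.5 and 85% at 1. The article has no variance components with which to choose among these.

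It would go too far to say that the trial has 56% power, that it is underpowered, or that the 85% was miscalculated. The first two need inputs that the article does not give, and the third cannot be checked. What can be said is that the power of the co-primary tests is unstated and that the published figure does not stand in for it.

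**What to change.** 1. Define accuracy (proportion of correct reads, or AUC) and say whether the 10% is absolute or relative.
2. Reconcile the two statements of the primary outcome under Statistical analyses, so that one set of primary measures remains.
3. Rerun the same multi-reader program with 18 readers, once for patient-wise sensitivity on 250 fracture images and once for patient-wise specificity on 250 normal images, at the alpha used for each. State the variance inputs and show a range around the pneumothorax-derived values.
4. Replace the 85% sentence and the assurance of sufficient power with the resulting power, or minimum detectable difference, for each co-primary.

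The cost is one rerun of software already in use and some rewording. No extra readers or images are needed, and the analysis model does not change. The downside is that the stated figure is likely to look less favourable.

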### Statistical analyses

The performance of the algorithm will be compared with the ground truth generated by the musculoskeletal radiologist panel. The continuous probability score from the algorithm will be used for the AUC analyses, while binary classification results with three different operating cut-offs will be used for evaluation of sensitivity, specificity, PPV and NPV. Sensitivity and specificity of readers with and without AI will be tested based on the Obuchowski-Rockette model for MRMC analysis which will model the data using a two-way mixed effects analysis of variance (ANOVA) model treating readers and cases (images) as random effects and effect of AI as a fixed effect with recommended adjustment to df by Hillis.^21^

The difference in diagnostic characteristics (sensitivity, specificity, accuracy, area under the receiver operating characteristic (ROC) curve) of readers as compared with ground truth with and without AI assistance will be the primary outcome on a per image and per abnormality basis. The main analysis will be performed as a single pooled analysis including all groups and sites. Secondary outcomes will include comparison between the performance of subgroups by specialty (emergency medicine, trauma/orthopaedics, physiotherapy, nurse practitioner, radiologist, radiographer), level of seniority (senior, middle grade, junior), degree of difficulty of the image and by anatomical region. Reader-reported confidence with and without the AI assistance will be compared. Secondary outcomes include the diagnostic characteristics of the AI algorithm alone. Surveys will be conducted throughout the study to measure the satisfaction, adoption and confidence in the AI algorithm of the study participants. Per-patient sensitivity will be defined as the proportion of reads in which all true fractures were marked as a proportion of the reads having at least one fracture. Per-patient specificity will be defined as the proportion of reads in which no fracture was marked by the reader as a proportion of the reads that did not show a fracture. These definitions disregard the detection of multiple fractures thus we will define the fracture-wise sensitivity as the proportion of fractures correctly detected as a proportion of all fractures. The two coprimary outcomes will be patient-wise sensitivity and patient-wise specificity. The stand-alone algorithm performance will be assessed by calculating the area under the curve (AUC) of the ROC and free-response ROC curves plotted with their variance. To account for correlated errors arising from readers interpreting the same images with and without AI, the Obuchowski and Rockette, Dorfman-Berbaum-Metz^22^ procedure; a modality-by-reader random effects ANOVA model will be used for estimation. Analyses will be carried out using R and the MRMCaov library.

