### Case selection and composition

The image dataset will include anonymised radiographs of adult patients (≥18 years) who presented to the EDs of OUH NHS Foundation Trust with a suspicion of fracture after injury to the limbs, pelvis or thoracolumbar spine. As CT is the investigation of choice for skull and many cervical spine injuries, these will be excluded from the study. Paediatric patients will be excluded from the dataset as their fracture types differ from those in adults, and there is an ongoing study evaluating this aspect (FRACTURE study; Fast Reporting using Artificial Intelligence for Children's TraUmaticRadiology Examinations^12^). Obvious fractures (defined as fractures including any of the following: displacement>5 mm, shortening>5 mm or angulation>5°) will also be excluded.

To constitute the dataset, radiology reports will be screened from the radiology information system to develop an enriched dataset of the 500 standard clinical examinations evenly split between normal and abnormal, with one or more fractures. The ratio of radiographs from each anatomical location has been informed by the proportion of missed fractures mentioned in the NHS Resolution report (table 1).

**Table 1 T1:** Proportion of radiographs of each anatomical location, based on the proportion of missed fractures mentioned in the National Health Service Resolution report

Body part	Images in the dataset, n
Spine	42
Shoulder	20
Elbow	20
Wrist/hand	150
Hip/pelvis	130
Knee	42
Foot/ankle	96

To ensure a like-for-like comparison, image finding for abnormal cases will be performed first. The normal images will be age and sex matched per body part. We will aim to include representation of the different image views, system type (mobile or fixed), system vendors and patient demographics (eg, age, sex) without any prespecified quota.

The dataset will then be anonymised and uploaded to the Report and Image Quality Control platform under an existing data governance approval from the OUH NHS Foundation Trust Caldicott guardian.

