### Strengths and limitations

This study uses a CE (Conformité Européenne)-marked AI-assisted fracture detection algorithm with an NHS-derived dataset. The enhanced dataset will allow evaluation of a broad range of pathologies, including rare but significant fractures and its composition is mapped to mirror the proportions of missed fracture locations seen in the NHS Resolution report. A broad set of health professionals will be recruited as participants, including under-represented groups such as nurse practitioners and physiotherapists, from multiple hospital sites across the region—these reflect a reader group not yet explored in the literature, and one directly applicable to the NHS.

In terms of limitations, while the overall study group is large in comparison to other similar reader studies, the small number of readers in subgroups may reduce the statistical power for comparison between professional groups. The dataset will include an abnormally high disease prevalence (50%) to include a broad range of pathologies to facilitate meaningful statistical comparison, meaning that while the reader study will effectively explore the impact of the algorithm on readers interpreting a broad and detailed dataset, the results will not mirror the prevalence of pathologies encountered in normal clinical practice and further prospective study will be required to determine efficacy in this regard.

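### Accuracy is listed as primary and is the measure named in the power statement, yet it is undefined, is not one of the two coprimaries, and as a per-image proportion is specific to a 50% fracture set

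*Protocol article*

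**What the plan says.** All places are in the protocol article.

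- **Statistical analyses, first statement of the primary outcome:** "The difference in diagnostic characteristics (sensitivity, specificity, accuracy, area under the receiver operating characteristic (ROC) curve) of readers", with and without AI, per image and per abnormality. Accuracy stands here as a measure distinct from sensitivity, specificity and AUC.
- **Statistical analyses, later statement:** the two coprimary outcomes are patient-wise sensitivity and patient-wise specificity. The same section names sensitivity and specificity as the reader measures to be tested in the Obuchowski-Rockette model.
- **Sample size and power calculation:** the only stated power is "85% power to detect a 10% difference in accuracy between unassisted and AI-assisted readings", "with a 5% type 1 error rate", for 18 readers and 500 cases. The inputs are "Based on parameters derived from our previous MRMC study on pneumothorax detection".
- **Outcome measures:** sensitivity, specificity, PPV, NPV and AUC are listed. Accuracy is not, and no section defines it.
- **Case selection and composition:** the 500 examinations are "evenly split between normal and abnormal, with one or more fractures".
- **Strengths and limitations:** the 50% prevalence is declared abnormally high, and "the results will not mirror the prevalence of pathologies encountered in normal clinical practice". The remark is general and is not tied to the accuracy measure.

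**The concern.** The article gives two different primary lists and a power statement that matches only the first. Accuracy is in the first list and in the power statement, but not among the coprimaries. A report could therefore present an accuracy gain as a primary result on the powered measure and still be following the text.

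That matters because accuracy, read as the proportion of images classified correctly, mixes sensitivity and specificity in proportion to the share of fracture images. The investigators set that share. At an even split, one point of sensitivity gained offsets one point of specificity lost. Where fractures are rarer, specificity carries more weight and the same reader behaviour gives a different accuracy difference. Sensitivity and specificity reported separately are not weighted in this way.

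The setting makes a specificity loss worth guarding against. The Introduction raises automation bias, and the last study aim is to measure errors made when the AI is wrong. A false alert followed on a normal film lowers specificity. The same bias can also lower sensitivity when the AI misses a fracture, so the direction cannot be presumed.

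**Working it through.** **Inputs from the article.** 500 images, evenly split, so 250 with and 250 without fracture (taking the planned split to hold after the reference reading); 18 readers, each reading all 500; a 10-point accuracy difference; 85% power; 5% type 1 error, assumed two-sided.

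**Inputs not in the article.** Fracture prevalence among ED radiographs; expected changes in Se and Sp; baseline accuracy; variance components. The nearest prevalence figure, in the Introduction, is 5.1% of all ED attendances for fractures or dislocations. Its denominator is attendances, not radiographs, so it cannot be used. The changes and prevalences below are assumptions.

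**Step 1: the plan's own figure.** The 85% cannot be reproduced, because the text gives neither the program's inputs nor its output. It can only be turned into an implied standard error of the AI difference:
- normal approximation: 0.10 / (1.960 + 1.036) = 0.0334;
- noncentral F with 17 denominator df (18 readers minus 1): 0.0314.

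Neither value shows which measure was powered.

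**Step 2: what accuracy is in this set.** With fracture share p, per image,

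accuracy = p × Se + (1 − p) × Sp, so change in accuracy = p × ΔSe + (1 − p) × ΔSp.

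At p = 250/500 = 0.5 this is (ΔSe + ΔSp)/2. If the powered measure is per-image accuracy, 10 points means ΔSe + ΔSp = 20 points. The identity does not describe a per-abnormality measure.

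**Step 3: dependence on p.** If ΔSe > 0 and ΔSp < 0, the sign changes at p* = |ΔSp| / (ΔSe + |ΔSp|). Changes are in percentage points:

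| Assumed ΔSe / ΔSp | 50% | 30% | 20% | 10% | Break-even p* |
|---|---|---|---|---|---|
| +10 / −2 | +4.0 | +1.6 | +0.4 | −0.8 | 2/12 = 16.7% |
| +10 / −4 | +3.0 | +0.2 | −1.2 | −2.6 | 4/14 = 28.6% |
| +10 / −5 | +2.5 | −0.5 | −2.0 | −3.5 | 5/15 = 33.3% |
| +25 / −5 | +10.0 | +4.0 | +1.0 | −2.0 | 5/30 = 16.7% |
| +20 / 0 | +10.0 | +6.0 | +4.0 | +2.0 | none |

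Example, second row at 20%: 0.2 × 10 + 0.8 × (−4) = 2.0 − 3.2 = −1.2.

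The last two rows both equal the 10-point target at 50%. One turns negative below 16.7%. The other keeps its sign but falls to +4.0 at 20%. The size therefore depends on the sampling ratio even without a specificity loss. The sign depends on it only with one.

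**The case against.** The other side has four good points.

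1. **The coprimaries already protect the conclusion.** Patient-wise sensitivity and specificity are named as coprimary, and those two measures are named for the formal reader-model test. A reader might infer that a specificity loss would be hidden inside an accuracy gain. The article does not support that: the loss would show in its own coprimary. This point stands, and it limits the harm. It does not take accuracy out of the first primary list or the power statement.

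2. **The powered accuracy may not be the proportion correct.** The word is undefined, is absent from Outcome measures, and is used loosely elsewhere for diagnostic performance. The program's figure of merit could be AUC, which is not weighted by prevalence. This also stands: one cannot say that the study is powered on a prevalence-weighted measure, only that the text leaves it open. In the primary list, however, accuracy appears beside AUC and so must be something else.

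3. **The enrichment is declared.** Strengths and limitations says further prospective study is required. That is fair disclosure, but it does not tell the reader that accuracy depends on the 50% share in a way that sensitivity and specificity do not.

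4. **Re-weighting would not yield ED accuracy.** The set excludes obvious fractures, takes its body-part mix from a report on missed fractures, and matches normals on age and sex. Sensitivity and specificity from that spectrum, multiplied by an ED prevalence, could suggest a transportability that is not there. This stands. It is a reason to keep any re-weighted table illustrative and not to make permitted claims depend on it.

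**Conclusion.** The point holds as a conflict over what is primary, made consequential by the sampling ratio. The article names four primary measures, then two, and states power for a term it does not define. If accuracy means the proportion of images classified correctly, its AI difference in this set is (ΔSe + ΔSp)/2 and should not serve as a primary result.

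The size cannot be fixed from the article. Under the assumed changes, a gain of 2.5 to 4.0 points at 50% becomes between +0.4 and −2.0 points at 20%. A full 10-point gain becomes +1.0 or +4.0 there, depending on how it is made up.

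A reader might go further and infer that the study would declare AI better when it lowers accuracy in EDs. The article does not support that. A reversal needs both a specificity loss and an ED prevalence below the break-even, and neither is given. No rule in the text ties the conclusion to accuracy alone.

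The arithmetic assumes per-image scoring and a final split of 250 to 250.

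**What to change.** - **Statistical analyses:** delete accuracy from the first list of primary measures and state that the conclusion rests on the two coprimaries, patient-wise sensitivity and patient-wise specificity. AUC is not weighted by prevalence and is not affected by this point, but its status should be made explicit in the same edit.
- **Accuracy, if reported:** make it secondary and per image, labelled as balanced accuracy, (Se + Sp)/2, in a set with 50% fractures. Optionally add an illustrative table of p × ΔSe + (1 − p) × ΔSp over a stated range of p, with the break-even prevalence and the caveat that the case spectrum is also selected.
- **Sample size and power calculation:** state which measure the 85% refers to and align it with the coprimaries. Each coprimary rests on its own half of the set, 250 images, not on all 500.

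**Cost.** Changes of wording, at most one table from estimates already planned, and a rerun of the sample size program if the powered measure was not a coprimary. No new images, reads or readers. The downside is a less simple headline figure, and power for the coprimaries may turn out to differ from 85%.

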Over the last decade, advances in computer vision and machine learning have been used to augment interpretation of medical imaging.^10^ Several artificial intelligence (AI) algorithms have been developed that are able to detect fractures on plain radiographs with a high degree of accuracy.^11^ One such algorithm is the Gleamer BoneView (Gleamer, Paris, France) (see figure 1), which is currently the mostly widely used fracture detection algorithm in the NHS as well as worldwide (>800 sites in 30 countries). This algorithm estimates the likelihood of a fracture being present on a radiograph and provides users with three outcomes: *fracture*, no *fracture* and *uncertain*. If the likelihood has been estimated to be above a designated cut-off value, the area of abnormality is highlighted as a region of interest on a secondary image, which is made available to clinicians via their picture archive and communication system. If no abnormality is detected, this is also stated on the secondary image.^12 13^ Prior studies have demonstrated that the algorithm is highly accurate at detecting abnormalities, and it is already in use in a number of European centres, having received regulatory approval for use to support clinicians interpreting plain radiographs. Previous research has suggested that the algorithm is highly accurate at detecting abnormalities, and it is already in use in a number of European centres, having received regulatory approval for use to support clinicians interpreting X-rays. Moreover, recent studies have suggested that the use of AI software for detecting bone fractures^14 15^ can drastically decrease the rate of missed fractures. However, this software has not yet been fully tested in a UK setting using a locally derived dataset, and it is unclear to what degree such systems would affect the diagnostic performance of certain staff groups specific to the NHS, such as reporting radiographers and specialist nurse practitioners.

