### Study aims

To evaluate the impact of AI-enhanced imaging on the diagnostic performance, efficiency and confidence of clinicians in detecting fractures on plain radiographs (primary).To determine the stand-alone diagnostic accuracy of the BoneView AI tool with respect to the reference standard (secondary).To determine associations between professional background and level of experience when determining the impact of AI support on clinician fracture detection (secondary).To explore which imaging factors influence clinicians’ reporting accuracy and efficiency, and algorithm performance, for example, category of abnormality, size of abnormality, image quality, presence of multiple abnormalities (secondary).To measure whether clinicians are more likely to make a mistake when AI provides an incorrect diagnosis (secondary).

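### One of the secondary stand-alone AI measures, the area under the free-response ROC curve with no limit on false marks, is unbounded and rises as false marks are added

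*Protocol article*

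**What the plan says.** Stand-alone accuracy of the algorithm is a declared secondary aim (Study aims: "To determine the stand-alone diagnostic accuracy of the BoneView AI tool with respect to the reference standard (secondary") and a secondary outcome (Statistical analyses: "Secondary outcomes include the diagnostic characteristics of the AI algorithm alone").

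The Statistical analyses section gives these measures:

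- For the areas: "The continuous probability score from the algorithm will be used for the AUC analyses".
- For the binary results: "binary classification results with three different operating cut-offs will be used for evaluation of sensitivity, specificity, PPV and NPV".
- For the summary of the algorithm alone: "calculating the area under the curve (AUC) of the ROC and free-response ROC curves plotted with their variance".

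The article mentions FROC nowhere else. It gives no maximum number of false marks per image, no partial area and no bounded variant. The three operating cut-offs are tied to the binary measures, not to a limit on the FROC axis. On how the device emits marks, the Introduction says: "If the likelihood has been estimated to be above a designated cut-off value, the area of abnormality is highlighted as a region of interest".

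**The concern.** A ROC curve lies in a unit square, so its area is a probability between 0 and 1. A FROC curve does not. Its vertical axis is the fraction of fractures correctly localised, which cannot exceed 1. Its horizontal axis is the mean number of false marks per image, which starts at 0 and ends wherever the algorithm stops marking. An area taken to that end point mixes detection with the length of the axis, and more false marks make the axis longer.

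If the sentence is followed as written, the report will contain a FROC area with no fixed scale. It cannot be set beside the ROC area in the same sentence or beside a FROC area from elsewhere, and it moves in the wrong direction when the algorithm makes more false marks. Its sampling variance can be estimated, but that does not make the quantity a measure of accuracy.

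**Working it through.** The article states no FROC figure, so there is nothing to reproduce. The check is of the measure itself.

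**Step 1: the direction follows from the axes.** Let N be the number of images, s_j the score of false mark j, and F(s) the fraction of all fractures that are marked with a score above s. Without ties, the empirical area up to the observed end point is

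area = (1/N) × Σ_j F(s_j).

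Every term is between 0 and 1. Adding a false mark therefore never lowers the area, and raises it whenever any fracture scores higher than that mark. The only ceiling is the number of false marks per image. With N = 500 ("The study’s sample size of 500 images, evenly split between normal and abnormal cases"), one extra false mark that scores below 90% of the fractures adds 0.9/500 = 0.0018. No assumption about the algorithm is needed for this step.

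**Step 2: illustration of size.** The article gives no lesion scores and no false-mark rate, so these inputs are assumptions: 250 normal and 250 abnormal images, one fracture per abnormal image, fracture scores N(2,1), false-mark scores N(0,1), and a Poisson number of false marks per image. There were 200 replicates per rate. Fracture scores have the same distribution in every row.

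| False marks per image | Full FROC area | ROC area | AFROC area | FROC area up to 0.1 false marks |
|---|---|---|---|---|
| 0.1 | 0.092 | 0.992 | 0.992 | 0.091 |
| 0.25 | 0.230 | 0.983 | 0.982 | 0.082 |
| 0.5 | 0.462 | 0.965 | 0.963 | 0.071 |
| 1 | 0.925 | 0.941 | 0.933 | 0.060 |
| 2 | 1.844 | 0.900 | 0.878 | 0.048 |
| 4 | 3.680 | 0.851 | 0.800 | 0.038 |

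The last column has a maximum of 0.1; in the first row it averages only replicates whose curve reached 0.1.

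A hand check agrees. The expected full area is the false-mark rate times P(fracture score > false-mark score) = rate × Φ(2/√2) = rate × 0.921. That gives 0.1 × 0.921 = 0.092, 1 × 0.921 = 0.921 and 4 × 0.921 = 3.684. Nearly all of the rise is axis length.

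**Step 3: different assumptions.** Let 10% of fractures never be marked and 20% of abnormal images hold two fractures. The expected area is then rate × 0.9 × 0.921 = rate × 0.829. At 0.2, 0.5, 1.0 and 2.0 false marks per image this is 0.17, 0.41, 0.83 and 1.66, and simulation gave the same to within 0.01. The AFROC area fell: 0.93, 0.90, 0.86, 0.80.

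**Step 4: dependence on the marking cut-off.** Take one algorithm with 4 candidate false marks per image and the Step 2 scores, and build the curve only from marks above a cut-off.

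| Cut-off | False marks per image at end point | Fractures localised | Full FROC area |
|---|---|---|---|
| 2 | 0.08 | 0.488 | 0.029 |
| 1 | 0.66 | 0.840 | 0.446 |
| 0 | 2.03 | 0.964 | 1.694 |
| −3 | 4.00 | 1.000 | 3.641 |

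The same algorithm yields any of these areas, depending on where marking stops. This matters if the FROC curve is built from emitted marks. The article does not say whether a score is available for regions below the device's cut-off.

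**Step 5: what removes the problem.** The AFROC area and the FROC area with a fixed limit both fall as false marks rise. Dividing the full area by its own end point does not help: the Step 2 ratio is 0.092/0.1 = 0.92 at the lowest rate and 3.680/4 = 0.92 at the highest, so it ignores the false-mark rate altogether.

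**The case against.** **The sentence may mean something else.** It can be read as an area for the ROC curve only, with FROC curves merely plotted. The Outcome measures section lists only the ROC area, which supports that reading. It is possible but less natural, because the area phrase governs both curves. If it is what the authors intend, a clarifying sentence is still needed.

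**The limit may be set elsewhere.** The Ethics and dissemination section says a detailed protocol is available on request, and a limit stated there would resolve the point. But the article names the measure without qualification, and the measure as named is ill-defined. That goes beyond leaving out detail.

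**It matters little.** Much of this stands, and several stronger readings should be set aside:

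- A reader might infer that the stand-alone aim rests on this area. It does not: the Outcome measures and Statistical analyses sections also give the algorithm's ROC area, and its sensitivity, specificity, PPV and NPV at three cut-offs. Poor specificity would show there.
- A reader might infer that no other planned measure uses fracture location. The fracture-wise sensitivity in the Statistical analyses section is not worded as applying to readers only, so it may do so.
- A reader might infer that the trial would make an over-marking tool look many times better. The study tests one fixed commercial tool, compares no FROC areas between tools or settings, and ties no decision to one. The simulated rates are not figures for this device.

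**Conclusion.** The point holds, at limited weight. On the natural reading of the Statistical analyses section, one stand-alone measure is a full FROC area. It has no upper bound, depends on where marking stops, and rises with false marks at unchanged fracture detection. It is not an interpretable accuracy figure.

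The direction and the lack of a bound follow from the definition of the axes. The sizes (0.092 to 3.680 over 0.1 to 4 false marks per image, and 0.029 to 3.641 for one algorithm across cut-offs) rest on assumed scores and rates and are illustrations only.

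The effect is confined to one of several secondary measures of the algorithm alone. It would be wrong to infer that the main result is affected. The article states: "The two coprimary outcomes will be patient-wise sensitivity and patient-wise specificity". Those are reader outcomes and do not use the FROC area. The correction should be made, but the trial's main conclusions do not depend on it.

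**What to change.** Reword the sentence on stand-alone performance in the Statistical analyses section to say that:

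- the area is calculated for the ROC curve, and the FROC curve is a descriptive plot;
- the location-sensitive summary is a bounded measure, either (a) the AFROC figure of merit, weighted for images with several fractures, or (b) the FROC area, or the fraction of fractures detected, up to a number of false marks per image fixed before analysis;
- its variance comes from a jackknife or bootstrap that resamples whole images.

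Either option serves, and the choice is partly preference. Under (b), the limit must lie within the range that the emitted marks cover, so the plan should say whether scores are available for regions below the device's cut-off.

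The cost is one sentence and a few extra lines of analysis code. The algorithm's scores and marks and the radiologists' bounding boxes are already planned; no new images or reads are needed.
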